## Abstract

*Streptococcus pneumoniae* is the leading cause of morbidity and mortality due to community acquired pneumonia, bacterial meningitis and bacteraemia worldwide. Pneumococcal conjugate vaccines protect against invasive disease, but are expensive to manufacture, limited in serotype coverage, associated with serotype replacement and demonstrate reduced effectiveness against mucosal colonisation.  As asymptomatic colonisation of the human nasopharynx is a prerequisite for pneumococcal disease, this is proposed as a marker for novel vaccine efficacy. Our team established a safe and reproducible pneumococcal controlled human infection model at Liverpool School of Tropical Medicine (LSTM). This has been used to test vaccine induced protection against nasopharyngeal carriage for ten years in over 1000 participants.

We will transfer established standardised operating procedures from LSTM to Malawi and test in up to 36 healthy participants. Primary endpoint: detection of the inoculated pneumococci by classical culture from nasal wash recovered from the participants after pneumococcal challenge. Secondary endpoints: confirmation of robust clinical and laboratory methods for sample capture and processing. Tertiary endpoints: participant acceptability of study and methods. We will test three doses of pneumococcal inoculation (20,000, 80,000 and 160,000 colony forming units [CFUs] per naris) using a parsimonious study design intended to reduce unnecessary exposure to participants. We hypothesise that 80,000 CFUs will induce nasal colonisation in approximately half of participants per established LSTM practice.

The aims of the feasibility study are: 1) Establish
*Streptococcus pneumoniae* experimental human pneumococcal carriage in Malawi; 2) Confirm optimal nasopharyngeal pneumococcal challenge dose; 3) Confirm safety and measure potential symptoms; 4) Confirm sampling protocols and laboratory assays; 5) Assess feasibility and acceptability of consent and study procedures. Confirmation of pneumococcal controlled human infection model feasibility in Malawi will enable us to target pneumococcal vaccine candidates for an at-risk population who stand the most to gain from new and improved vaccine strategies.

## Abbreviations

AE: Adverse Event; CAP: Community Acquired Pneumonia; CFU: Colony Forming Units; CHIM: Controlled Human Infection Model; CRF: Case Report Form; DSMB: Data, Safety and Monitoring Board; EHPC: Experimental Human Pneumococcal Colonisation; ELISA: Enzyme-Linked Immunosorbent Assay; ELISPOT: Enzyme-Linked Immune Absorbent Spot; FBC: Full Blood Count; GCP: Good Clinical Practice; HIV: Human Immunodeficiency Virus; HTS: Human immunodeficiency virus Testing Service; ICH-GCP: International Conference on Harmonisation of Good Clinical Practice; LSTM: Liverpool School of Tropical Medicine; MARVELS: Malawi Accelerated Research in Vaccines, Experimental and Laboratory Systems; MHRA; Medicines and Healthcare products Regulatory Authority (UK Regulator); MK: Malawian Kwacha; MLW: Malawi-Liverpool Wellcome Trust Clinical Research Programme Laboratories; MTA: Material Transfer Agreement; NHSRC: National Health Sciences Research Committee; OM: Otitis Media; PBMC: Peripheral Blood Mononuclear Cell; PCR: Polymerase Chain Reaction; PCV: Pneumococcal conjugate vaccines; PCV13: Pneumococcal conjugate vaccine 13; PCVPA: Pneumococcal Carriage in Vulnerable Populations in Africa; PMPB: Pharmacy, Medicines and Poisons Board; QECH: Queen Elizabeth Central Hospital; RNA: Ribonucleic Acid; SAE: Serious Adverse Event; SOP: Standardised Operating Procedure; SUSAR: Serious Unexpected Serious Adverse Reaction; TSC: Trial Steering Committee.

## Introduction

*Streptococcus pneumoniae* is the leading cause of morbidity and mortality due to community acquired pneumonia (CAP), bacterial meningitis and bacteraemia worldwide
^1^. Pneumococcal infections cause over one million pneumonia deaths per year in children in the developing world and are also a major burden of otitis media globally. Pneumococcal conjugate vaccines (PCV) represent a great achievement in providing protection from invasive pneumococcal disease, but they are expensive to manufacture, limited in serotype coverage, associated with serotype replacement and are less effective against mucosal infection (13–20%) than against invasive disease
^2^. Alternative vaccine strategies are therefore still urgently needed
^3^ and several promising vaccine alternatives are being developed worldwide.

A major roadblock to the process of developing new protein vaccines has been a means of prioritising between proposed vaccine candidates
^4^. Because asymptomatic colonisation of the human nasopharynx is a prerequisite for pneumococcal disease, it has been proposed as a marker for vaccine efficacy
^5^. We established a safe and reproducible Controlled Human Infection Model (CHIM) at Liverpool School of Tropical Medicine (LSTM), U.K., which has been used to test the protection induced by vaccination against nasopharyngeal carriage
^6^. The Liverpool CHIM, also known as Experimental Human Pneumococcal Carriage (EHPC), established over the last ten years, uses a serotype 6B pneumococcal strain to establish carriage in 50% of healthy participants after nasopharyngeal challenge with 80,000 bacterial colony forming units presented to each nostril (naris) in 100 µl of saline. This model has been used to test the effect of new candidate vaccines with significant cost and time savings compared with phase III trials
^6^.

Despite the introduction of the PCV13 vaccine to Malawi in 2011, pneumococcal disease remains the single most important bacterial infection of adults and children
^7^. Long term follow-up has been rigorously carried out by the Pneumococcal Carriage in Vulnerable Populations in Africa (PCVPA) consortium
^8^. These data demonstrate that despite an impressive reduction in invasive pneumococcal disease for vaccinated children, there is persistent nasal carriage of both vaccine type and non-vaccine type
*Streptococcus pneumoniae* in both children and HIV-infected adults (
Table 1). The implications of this important finding are that (A) herd effects with PCV13 are not as strong as in Malawi compared to US data, with vaccine type pneumococcus a continued threat to vulnerable adults and children and (B) the persistent pneumococcal carriage may indicate sub-optimal or short duration of PCV13 vaccine-induced immunity. There is therefore an urgent need for new vaccines in Malawi and EHPC may offer a means to choose among alternative novel vaccines.

**Table 1. T1:** Pneumococcal Carriage in Vulnerable Populations in Africa (PCVPA) consortium data from 2018 on pneumococcal carriage and pneumococcal conjugate vaccine 13 status
^8^. The data show that despite vaccination, children aged 3–6 years have the same vaccine type carriage rates as unvaccinated 5–10-year olds.

Malawian PCVPA surveillance data	Children 3–6 years (PCV vaccinated)	Children 5–10 years (not PCV vaccinated)	HIV infected adults (not PCV vaccinated)
Vaccine type carriage	20.1% (95% CI: 18.0, 22.3)	20.1% (95% CI: 17.5, 22.9)	13.9% (95% CI:11.8, 16.2)
Non-vaccine type carriage	55.9% (95% CI: 53.3, 58.6)	36.8% (95% CI: 33.6, 40.0)	29.5% (95% CI: 26.7, 32.5)

A valid criticism of current vaccine research strategies is that these have been conducted in geographical areas and participant populations not at significant risk of disease. To address this, we propose to transfer our safe and established standardised operating procedures from the Liverpool CHIM to the Malawian setting. The Liverpool CHIM has been used in over 1000 healthy adults for the past nine years safely with no cases of active infection or related serious adverse effects. A Malawian pneumococcal CHIM will allow targeted pneumococcal vaccine candidate choices to be made based on relevant pathogen challenge in an at-risk population who stand the most to gain from new and improved vaccine strategies.

### Ethical considerations for controlled human infection studies in low income settings

The ethical considerations for CHIM studies and for experimental human pneumococcal carriage in particular were extensively explored at a workshop in Malawi from which a guideline summary was published
^9^. Further consideration of this topic was presented at an ASTM&H symposium in New Orleans, 2018. Briefly, the benefit of vaccine development in the target population has been overwhelmingly demonstrated by the malaria programme and further benefit is expected for vaccines deployed in populations with high exposure. The ethical principles governing CHIM studies are no different in low income countries than anywhere else but the operational challenges to ensure participant safety may involve more health services support than in highly resourced settings. Appropriate consent requires a high level of participant involvement and comprehension in any context - this may also require additional effort in settings where participants have experienced limited science education. The detailed consideration of community knowledge and views regarding the CHIM of pneumococcal carriage in Malawi will shortly be published (IN PRESS: BMC Medical Ethics
^10^).

## Study protocol

### Study aims

The aims of this study are:

1. Establish controlled human infection with
*Streptococcus pneumoniae* serotype 6B in Malawi2. Confirm nasopharyngeal pneumococcal challenge dose required to establish ~50% carriage in Malawian participants3. Confirm safety and measure potential symptoms of controlled human infection procedures for study participants4. Confirm sampling protocols and laboratory assays for immunological assessment relevant to vaccine testing.5. Assess the feasibility and acceptability of consent and study procedures for participants.

### Study hypothesis

That inoculation of Malawian volunteers with 80,000 cfu/naris will safely result in nasopharyngeal carriage in ~50% of participants as it has done in Liverpool.

### Study design

A feasibility study of adult healthy human participants experimentally exposed to escalating doses of
*Streptococcus pneumoniae* in the nasopharynx to determine optimal dosage for establishment of nasal carriage. We will closely monitor study participants to ensure safety and tolerability of study procedures. We will measure immune protective responses to
*Streptococcus pneumoniae* challenge using mucosal (nasal, throat and salivary) and blood samples to determine assay feasibility.

The study will be carried out in four stages:

1. Screening and recruitment: Potential participants will be screened to ensure health and safety as detailed in Methods.

2. Inoculation with pneumococci: Participants will be randomly allocated to inoculation with
*Streptococcus pneumoniae* serotype 6B or 0.9% saline (sham inoculation) to the inside of each naris. Participants will be monitored for safety and establishment of carriage. The dose escalation schedule is described in
Figure 2.

3. Detection of pneumococcal carriage: Nasal wash samples will be taken, according to a standardized protocol
^11^, at days 2, 7, and 14 days post inoculation. Classical microbiological culture will determine nasal colonisation with pneumococcal serotype 6B at each time point.

4. Immunology response measurements: exploratory blood, mucosal and nasal cell samples will be taken to confirm robust clinical and laboratory standard operating procedures and explore the immunological response to nasal challenge.

### Study endpoints

Primary endpoint: detection of the inoculated pneumococci by classical culture methods, at any time point, from nasal wash recovered from the participants at days 2, 7 and 14 following pneumococcal challenge.

Secondary endpoints: confirmation of robust clinical and laboratory methods for sample capture and processing. Acceptability of study and methods.

### Study setting

Clinical procedures will be conducted at the Queen Elizabeth Central Hospital Research Ward, Blantyre, Malawi. Laboratory procedures will be conducted at the adjacent Malawi-Liverpool Wellcome Trust Clinical Research Programme Laboratories (MLW).

### Recruitment target

A maximum of 36 healthy adult participants will be recruited to complete the study.

### Duration

Recruitment of all participants and follow up will be completed within 12 months. 

### Participants, schedule and timelines

We will inoculate healthy non-smoking adult participants with a well-characterised, fully sequenced penicillin-sensitive pneumococci and observe them for the development of pneumococcal carriage up to 14 days post inoculation. Study discharge will occur on day 20.

Study visits must take place according to the proposed schedule to ensure participant safety. This will be clearly explained to the participants during recruitment and consent. If a participant is unable to comply, they will not be recruited (Participant flow chart -
Figure 1).

**Figure 1. f1:**
[figure not shown]
Participant flow chart. D-5 refers to 5 days before day 0, the day of inoculation, and d1 is one day after and so on. *The decision for antibiotics will be communicated directly at visit 7 except in the unlikely circumstance that only d14 is positive for carriage, in which case the result will be telephoned in time for visit 8.

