### Screening and preliminary assessment

Following consent, inclusion and exclusion criteria, data and samples will be collected.

• Clinical examination - the initial clinic visit will include a focused clinical history and targeted clinical examination involving auscultation of the lung fields and heart sounds. Participants will be informed if their clinical examination is normal. Should a previously unrecognised abnormality be identified, this will be explained to the individual, and appropriate investigations and follow-up will then be arranged by the study team. Further participation will be determined at the discretion of the study doctor dependent on the nature of the abnormality detected. If the participant is not eligible due to an acute illness, they may be re-screened at a later date with their verbal consent.

•
*Nasal wash* - will be performed using our published method
^11^. This is a well-used and validated technique to collect nasal bacterial specimens used successfully by the Liverpool CHIM team who will rigorously train the Malawi team. Briefly, 5ml of sterile saline is instilled and held for a few seconds in the nares before being expelled into a sterile Galli pot. This is repeated twice in each naris using 20ml saline in total. In the event of nasal wash loss (defined as cough/sneeze/swallow), the procedure may then be repeated to obtain an adequate specimen. Should the nasal wash reveal natural colonisation of pneumococcus, the participant will continue in the study and receive the inoculation as per protocol, unless the natural serotype is identified as 6B, in which case the patient then leaves the study at day 2. All pneumococcal carriage negative participants will continue in the study.

•
*Nasosorption strips* - Nasosorption will be obtained before a nasal wash and/or inoculation. The strips are like blotting paper developed by Hunts Development Ltd (UK, catalogue number: NSFL-FXI-11). They collect concentrated nasal lining fluid before the nasal wash to measure inflammatory responses induced by infection that may be associated with increased colonisation density and acquisition. Concentrate nasal fluid will be used to measure cytokine levels by multiplex bead array. Blotting paper will be held inside the nostril for up to 3 minutes until soaked, removed and placed in the microcentrifuge tube for storage.

•

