***Inoculation***

• Inoculation - using a P200 micropipette, 0.1ml saline containing the desired dose (see
Figure 2) of pneumococcus will be instilled into the nose. The participant will be seated in a semi-recumbent position. After inoculation, the participant will remain in this position for up to 15 mins. They will be given a post-inoculation advice sheet (including emergency contact details), thermometer, a course of amoxicillin (500mg TDS for 3 days) and a daily symptom log to complete.

• Dose escalation and sham inoculation - We have adopted a step-wise approach to escalating the inoculation dose. The protocol is designed to: a) minimise the possibility that we try repeatedly to attain carriage at a dose in which it is unlikely to occur; b) maximise safety by inoculating small groups (in case adverse events occur) before continuing on to larger groups in which we will be able to give reasonable precision to estimate carriage rates. Groups 1, 2 and 3 will receive increasing doses of pneumococcal inoculation as explained in
Figure 2. Briefly, 20,000 cfu/naris (Group 1) is not expected to achieve carriage. If 80,000 cfu/naris achieves more than 4 from 9 participants with carriage, then the study will end at that point. Sham inoculation with 0.9% normal saline has been incorporated into the study design to assess whether any potential observed effects in participants are pneumococcal challenge-related or simply reflect the study conditions. Participants will receive only one inoculation dose. If carriage is not achieved after inoculation, participation will be concluded upon completion of visit eight.

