### Randomisation

Randomization has been included to prepare (test feasibility) for future vaccine studies. The clinical team and participants will be blinded to the allocation to avoid bias in the collection and evaluation of data during the study. The randomisation code will be produced by the MLW Statistical Support Unit (co-investigator [name]) using a computer-generated pseudo-random permutation procedure. Prior to the start of the study, a copy of the randomisation code will be supplied to the MLW laboratory team using sealed envelopes to enable the production of
*Streptococcus pneumoniae* inoculations and sham inoculations as required by the randomisation schedule. The laboratory team will not be blinded to the challenge allocation, this measure is to ensure participant safety and monitoring during follow up. Research team members will be assigned solely to one of two separate delegation logs for blinded and unblinded activities (clinical and laboratory).

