### Termination of carriage

All study participants who are nasally colonised with pneumococcus at the end of the study will be asked to take oral amoxicillin 500mg three times daily for 3 days. This will be communicated at visit 7, or by telephone in the unlikely event of only visit 7 samples (day 14) showing carriage.

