### Sample size justification

This is a feasibility study that transfers a proven existing technique therefore we have not formally calculated power to detect the carriage rate. The study protocol and sample size are based on our previously published study demonstrating 50% nasal carriage at the 80,000 CFU dose in Liverpool, UK
^13^. This feasibility study is designed to determine if experimental pneumococcal nasal carriage is possible in the Malawian setting.

The primary endpoint is the occurrence of pneumococcal colonisation determined by the presence of pneumococcus in nasal wash samples at any time point post inoculation detected using classical microbiology.

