### Safety considerations and assessment

***Study design to ensure safety.*** Safety is paramount in human infection studies. While the risk to individuals of developing any infection is very low (40% Malawian adults experience natural colonisation at any time, and the incidence of invasive disease is 20/100 000 patient years
^5^), the study is designed to ensure any risk is minimal by appropriate:

Study team selection and rigorous training in human challenge proceduresStudy design with staggered recruitment approach (sample size and dose)Careful serotype selection and dosing based on 10 years of LSTM experienceParticipant selection and exclusion criteria as detailedParticipant education through a participant information sheet (provided)Rigorous safety procedures including daily monitoring and providing participants with a thermometer and a course of amoxicillin tablets in case of emergency
^14^
24-hour emergency telephone contact with researchers, including close individual daily monitoring, and access to hospital facilities and prompt treatment if requiredTo further mitigate risk, participants will be provided with accommodation at the Grace Bandawe Centre for three nights immediately following nasal challenge. If a participant determines that it is not possible to stay at the Grace Bandawe Centre for three nights then a pragmatic approach to further study procedures will be taken. If the participant can demonstrate that they remain readily available by phone and accessible with transport, this need not affect the procedure. Twice daily checks could replace the resident period. In the Liverpool CHIM there is no resident period at all. If, however, the participant absconds or is intending to be uncontactable, then participation in the study will be stopped and antibiotics offered as at the end of the protocol.

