### Assessing acceptability

We need to understand acceptability of study procedures to participants to inform future CHIM study design. Feedback from participants will help to identify any areas where study design could be adjusted to ensure participants have a positive experience and to maximise their comfort. Brief exit interviews will be carried out with each participant at visit 8. Data collection will examine reasons behind decisions on participation; understanding of the trial purpose, procedures and risks and views on information provision; satisfaction with trial experiences; and any social impacts of participation (e.g. impacts on education, household relationships, livelihoods). Emerging findings will be communicated to the clinical team to inform ongoing procedures, with quick communication of areas needing immediate attention.

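### The visit 7 antibiotic message depends on carriage and partly unblinds participants and clinical staff before day 20 follow-up ends, although blinding is promised for the whole study

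*Protocol article*

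**What the plan says.** All references are to the protocol article.

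- **Randomisation:** "The clinical team and participants will be blinded to the allocation to avoid bias in the collection and evaluation of data during the study". Staff are placed on separate logs for blinded (clinical) and unblinded (laboratory) work. No exception or end date is given for the blind.
- **Figure 1 legend:** "The decision for antibiotics will be communicated directly at visit 7 except in the unlikely circumstance that only d14 is positive for carriage". In that exceptional case the result is telephoned before visit 8. The Termination of carriage section repeats this arrangement.
- **Termination of carriage:** "All study participants who are nasally colonised with pneumococcus at the end of the study will be asked to take oral amoxicillin". The rule is not limited to serotype 6B or to challenged participants, and no start date for the course is fixed.
- **Screening and preliminary assessment:** "Should the nasal wash reveal natural colonisation of pneumococcus, the participant will continue in the study and receive the inoculation as per protocol". The exception is natural 6B carriage, which leads to withdrawal.
- **Inoculation:** the sham arm is included "to assess whether any potential observed effects in participants are pneumococcal challenge-related or simply reflect the study conditions".
- **Participants, schedule and timelines; Assessing acceptability:** discharge is on day 20, and "Brief exit interviews will be carried out with each participant at visit 8".
- **Statistical analysis, Safety:** adverse events are listed at study end by type and inoculation group, sham included. Participant-reported symptoms are also listed. Nothing separates events before the visit 7 message from events after it.

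**The concern.** Carriage is the outcome that the challenge is meant to produce, so a message triggered by carriage carries information about allocation. It is given at day 14, and follow-up runs to day 20. The last 6 of 20 days (30% of calendar follow-up), and everything collected at visit 8, come after participants and clinical staff have received that information. The promise of blinding throughout data collection is therefore not one the schedule delivers.

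The sham arm exists to separate effects of the challenge from effects of taking part. It is small: 3 participants per completed dose group and 9 at most overall. A few late symptom reports, made or judged in the light of the message, can change how that contrast reads. If the antibiotic course is also taken before day 20, drug exposure in that window would be more common in challenged than in sham participants. The article says randomisation is included to prepare for later vaccine studies, so the actual end of the blind should be stated accurately.

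**Working it through.** **Inputs**

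- Allocation per dose: 6:2 in the first cohort and 3:1 in the second, so 9 challenged and 3 sham (Figure 2 legend).
- Experimental carriage, p: 50%, from the Sample size justification, "demonstrating 50% nasal carriage at the 80,000 CFU dose in Liverpool, UK". The Figure 2 legend gives 50–60%.
- Natural carriage, q: 40%, from Safety considerations and assessment, "40% Malawian adults experience natural colonisation at any time".
- Assumptions: p and q are independent, and natural non-6B carriage at follow-up equals the population figure. The population figure is not restricted to non-6B strains, so lower values of q are shown as well.

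**The plan's own figure.** 3 doses × (8 + 4) = 36, the stated maximum, made up of 27 challenged and 9 sham. The prior probability of having been challenged is 27/36 = 0.75.

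**Offer rates under the rule as written (any pneumococcus)**

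- Challenged: 1 − (1 − p)(1 − q) = 1 − 0.5 × 0.6 = 0.70, or 6.3 of 9.
- Sham: q = 0.40, or 1.2 of 3. The chance that at least one of 3 sham participants gets an offer is 1 − 0.6³ = 0.78.

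**What the message reveals (Bayes' rule)**

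- Overall offer rate: 0.75 × 0.70 + 0.25 × 0.40 = 0.525 + 0.10 = 0.625.
- Challenged given an offer: 0.525 / 0.625 = 0.84.
- Challenged given no offer: (0.75 × 0.30) / (0.75 × 0.30 + 0.25 × 0.60) = 0.225 / 0.375 = 0.60.
- Carrying the challenge strain given an offer: (0.75 × 0.5) / 0.625 = 0.60.

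**Range**

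| p | q | Offer, challenged | Offer, sham | P(challenged), offer | P(challenged), no offer |
|---|---|---|---|---|---|
| 50% | 40% | 70% | 40% | 0.84 | 0.60 |
| 60% | 40% | 76% | 40% | 0.85 | 0.55 |
| 50% | 20% | 60% | 20% | 0.90 | 0.60 |
| 10% | 40% | 46% | 40% | 0.78 | 0.73 |
| 50% | 0% | 50% | 0% | 1.00 | 0.60 |

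The 10% row is an assumed value for a dose that seldom produces carriage. The last row is equivalent to an offer made only to 6B carriers, a rule the article does not state. Where a participant is known to have been negative at baseline, the rows with lower q are the more relevant ones. The article does not say whether blinded staff see baseline cultures.

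**Timing, side by side.** The Figure 1 legend fixes when the decision is communicated: visit 7, or by telephone before visit 8. Termination of carriage ties treatment to carriage at the end of the study. Neither says when the course starts or whether the serotype is disclosed. The legend also implies that the visit 7 decision rests on washes before day 14, which sits awkwardly with a criterion set at the end of the study.

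**The case against.** The strongest objection is that the blind concerns allocation, and carriage is only correlated with allocation. Sham participants who carry natural strains receive the same message, and about half of the challenged are not expected to carry 6B. A shift from 0.75 to 0.84 is modest. This stands, and it limits the point to partial unblinding. A reader might infer that the message reveals who carries the challenge strain. The article does not support that: the rule covers any pneumococcus, and only about 0.60 of those offered treatment would carry 6B under the central assumptions.

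A reader might also infer that amoxicillin begins at visit 7 and so distorts the day 14–20 safety data. The text does not fix the start, so this is conditional. All participants also hold an emergency amoxicillin pack from inoculation, so exposure before visit 7 is possible in either arm.

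Third, the consequence is limited. The primary endpoint uses washes from days 2, 7 and 14, read by a laboratory that is unblinded by design. Safety output is descriptive, and no comparison of exit interviews by arm is planned, so no stated interview analysis is harmed. This stands too. A listing by inoculation group that includes sham will nevertheless be read as a comparison, which is the purpose given for the sham.

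Fourth, the analysis plan and data collection forms are not shown and may already split the listings or order the visit 7 forms. That is possible. The mismatch between the promised blind and the visit schedule is within the article and does not depend on them.

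**Conclusion.** The article promises blinding to allocation during the study but schedules a carriage-dependent message at day 14, with follow-up to day 20. Participants and clinical staff are partly unblinded for the final 6 days and visit 8. With p = 50%, q = 40% and independence, an offer raises the probability of having been challenged from 0.75 to 0.84, and no offer lowers it to 0.60. For positive natural carriage, the range examined for an offer is 0.78 to 0.90.

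It would go too far to say that the late data are neither blinded nor comparable with sham. The arms still overlap in who gets the message (70% against 40%), and non-carriers in both arms get no end-of-study course. A difference in drug exposure before day 20 remains a possibility, not something the text establishes. The primary endpoint is unaffected, as are day 0–14 safety data recorded before the message. The point is worth correcting because the sham contrast is small and the correction is cheap.

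**What to change.** Leave the antibiotic rule unchanged and make three changes.

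1. At visit 7, complete the day 0–14 symptom and adverse event review before any carriage-based message is given.
2. List adverse events and symptoms by inoculation group in two periods: onset before, and onset after, disclosure or the first dose of the end-of-study course, whichever is earlier. Base the comparison with sham on the first period.
3. In the Randomisation section, state that the blind is maintained up to the visit 7 message. Reconcile that section with the Figure 1 legend and the Termination of carriage section on which carriage result is disclosed (6B or any pneumococcus) and when the course starts.

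The cost is the order of the visit 7 forms, one extra split in the safety listings and a short change to the protocol text. The downside is that the blinded sham comparison is then stated to cover about 14 days instead of 20.
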